### Primary and secondary hypotheses-analysis plan

#### Analytic plan

Intent to treat analyses (ITT) will be used to examine the primary outcome. All participants randomized will be included in analysis and analyzed by original group assignment [38]. Mixed effects regression modeling, implemented via SAS PROC MIXED that incorporated a random intercept trend, will be used since this analytic approach includes all participants that have data available on at least one time point [39]. Missing values will not be imputed or discarded, rather they will be treated as missing in the analysis. The analysis will include the linear time effect, the main effect of condition and the time and condition interaction to examine whether the experimental condition resulted in greater changes in sun behavior than the control condition over time. Age will be included as a covariate in the analysis. Chi-square analyses will be used to examine the differences between two conditions for the use of indoor tanning and sunless tanning at baseline and then at 1-month follow-up. Only participants with complete data at both time points will be included in the chi-square analyses.

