**Methods and Design:**

This cluster randomized trial will examine whether a beach-based intervention that promotes sunless tanning as a substitute for sunbathing and includes sun damage imaging and sun safety recommendations is superior to a questionnaire only control group in reducing sunbathing frequency. Female beach visitors (N = 250) will be recruited from 2 public beaches in eastern Massachusetts. Beach site will be the unit of randomization. Follow-up assessment will occur at the end of the summer (1-month following intervention) and 1 year later. The primary outcome is average sunbathing time per week. The study was designed to provide 90% power for detecting a difference of .70 hours between conditions (standard deviation of 2.0) at 1-year with an intra-cluster correlation coefficient of 0.01 and assuming a 25% rate of loss to follow-up. Secondary outcomes include frequency of sunburns, use of sunless tanning products, and sun protection behavior.

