### Research goals

In the present study, the efficacy of a multi-component beach-based intervention that features sunless tanning among female beach visitors will be tested. The intervention will promote sunless tanning as a substitute for sunbathing and include sun damage imaging and sun safety recommendations. The primary outcome will be sunbathing at 1-, and 12-months follow-up and a questionnaire-only control group will be employed for comparison. Secondary outcomes will include frequency of sunburns, use of sunless tanning products, and sun protection behavior.

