### Sample size considerations and statistical analyses

#### Sample size

The two-arm cluster randomized trial is designed to have at least 80% power at a 5% significance level to test the hypothesized intervention effects at 1- and 12-months on the primary outcome: average time spent sunbathing per week. Means and standard deviations from our previous investigation were used for sample size estimate. With the proposed analytic method, we estimated the required sample sizes for three testing scenarios, i.e., changes between baseline and 1 month, changes between baseline and 12 months, and the joint test involving all three time points (see Table 1). Sample sizes were calculated using the method developed by Frison [36]. Given the possibility that individuals recruited in the same day may show correlation between each other (intra-cluster correlation or ICC), we adjusted the sample sizes with assumed intra-cluster correlation coefficient of 0.01 with method of Garrett [37]. We anticipate a relatively low level of dependency should it exist (ρ = .01) given that individuals at the beach on one day may not be strongly different from individuals visiting the same location the next day. The estimated minimum sample sizes are presented in the Table 1 with the assumed parameters, specifically, the expected mean difference between the two arms after intervention is assumed to be 0.75 and 0.70 hours sunbathing per week at 1 and 12 months, the within-subject correlation is assumed to be 0.50 at 1 month and 0.45 at 12 months. These estimates allow for withdrawal and loss to follow up of 15% and 25% at 1 and 12 months.

**Table 1 T1:** Sample size for three test scenarios for primary outcome: hours spent sunbathing per week

	Mean (SD)									
									
Test Scenarios	Control	Post-Intervention	Expected difference in mean	Within-subject correlation	No. of cluster (day)	Subject/cluster	Intra-cluster correlation	Minimum size/group	Dropout rate	Adjusted minimum total size
A (0–2 month)	2.10 (2.0)	1.35 (2.0)	0.75	0.50	16	12	0.01	94	0.15	**222**
B (0–12 month)	2.10 (2.0)	1.40 (2.0)	0.70	0.50	16	14	0.01	118	0.25	**314**
C (0–2–12 month)	2.10 (2.0)	1.38 (2.0)	0.72	0.50	16	9	0.01	66	0.25	**176**

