More specifically, the primary hypothesis will be tested using a linear mixed model with group (intervention, control) as a between subjects factor (fixed effect) and time (baseline, 1 month, and 1 year follow-up) as a within subjects factor. Sunbathing is the primary outcome variable. Secondary outcome variables including sun protection behavior, sunburns, and use of sunless tanning products will be examined in the same way. Because these dependent variables appear to be associated with different motivating variables, they are likely to be conceptually distinct and will be analyzed in separate models. Age will be entered as a covariate in both models because these factors are typically associated with the outcome variables [42]. Significant group by time interactions would be consistent with the primary hypothesis, such that the intervention group would engage in higher rates of sun protection and lower rates of sun exposure than the control group at 1- and 1-year follow-up, but not baseline. In exploratory analyses, ethnicity (White, nonwhite), and age will be entered as factors in the original model to determine differential response by these factors.

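### The primary outcome is given both a condition-by-linear-time test and a three-level time factor; a line does not fit the trial's assumed step effect, and the coding of time is not stated

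*Protocol article*

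**What the plan says.** The Analytic plan section describes the intention-to-treat analysis of the primary outcome as a mixed model with a random intercept, using everyone with data on at least one occasion. On time it says: "The analysis will include the linear time effect, the main effect of condition and the time and condition interaction".

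The Longitudinal analyses section states how the primary hypothesis will be tested. It uses a linear mixed model with group as the between-subject factor and "time (baseline, 1 month, and 1 year follow-up) as a within subjects factor". It expects the arms to differ at both follow-ups and not at baseline, and it applies the same approach to the secondary outcomes.

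Under Research goals, both follow-ups belong to the primary outcome: "The primary outcome will be sunbathing at 1-, and 12-months follow-up". The Sample size section says the trial is "designed to have at least 80% power at a 5% significance level", and the arm difference "is assumed to be 0.75 and 0.70 hours sunbathing per week at 1 and 12 months". Table 1 sizes three scenarios: baseline to the first follow-up (A), baseline to 12 months (B), and all three time points together (C). No scenario is a slope.

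**The concern.** A linear time effect with its interaction compares one slope per arm. A three-level factor with its interaction asks whether the arm difference changes at either follow-up. The null hypotheses and degrees of freedom differ, and neither model is labelled secondary or a sensitivity analysis.

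The linear version also sits badly with the trial's own hypothesis. The arm differences assumed at 0, 1 and 12 months are 0, 0.75 and 0.70 h: a jump, then a plateau. A line must spread the jump over the whole period and push part of it into the condition main effect, where it appears as a baseline difference that does not exist. An intervention that worked exactly as assumed could then be non-significant in one model and significant in the other, with nothing to say which result governs. The ambiguity carries over to the secondary outcomes.

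**Working it through.** **Inputs.** Effects 0, 0.75 and 0.70 h (Sample size); "standard deviation of 2.0" and N = 250 (Abstract); dropout 15% and 25%, ICC 0.01 (Sample size). For correlation: "the within-subject correlation is assumed to be 0.50 at 1 month and 0.45 at 12 months", although Table 1 prints 0.50 in every row. Not stated and therefore assumed: two-sided testing, 1:1 allocation, the 1-to-12-month correlation (0.45 or 0.50), the dropout pattern, and the coding of linear time. The age covariate is ignored.

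**Step 1: reproduce Table 1.** Baseline-adjusted formula at 80% power, with r follow-ups and m subjects per day:

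n = 2(1.96 + 0.84)² × SD²/δ² × [(1 + (r − 1)ρ)/r − ρ²] × [1 + (m − 1) × 0.01]

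- A (δ = 0.75, ρ = 0.50, r = 1, m = 12): 83.7 × 1.11 = 93; printed 94.
- B (δ = 0.70, ρ = 0.45, r = 1, m = 14): 102.2 × 1.13 = 115.5, so 116; printed 118.
- C (δ = 0.72, ρ = 0.50, r = 2, m = 9): 60.6 × 1.08 = 65.4, so 66; printed 66.

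From the printed sizes, 2 × 94/0.85 = 221.2 (printed 222), 2 × 118/0.75 = 314.7 (printed 314) and 2 × 66/0.75 = 176 (printed 176). So the sizing rests on post-baseline differences at 80% power, not on a slope.

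**Step 2: what a line does to the assumed effects.** Simplest case: equal correlation 0.50, complete data, 125 × 0.75 = 93.75 per arm, no design effect.

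*Time in months (0, 1, 12).* Mean 4.333, Sxx = 88.667, Sxy = (−3.333)(0.75) + (7.667)(0.70) = 2.867. Slope = 2.867/88.667 = 0.0323 h per month. Over 12 months this is 0.388 h instead of 0.70; at 1 month it is 0.03 h instead of 0.75. Intercept = 0.4833 − 4.333 × 0.0323 = 0.343 h, a spurious baseline gap. SE of the 12-month change = 12 × √[2 × 4 × 0.5/(93.75 × 88.667)] = 0.263, so z = 1.47 and power is 31%.

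*Time by wave (0, 1, 2).* Sxx = 2, slope = 0.70/2 = 0.35 per wave. The fitted last-visit change is 0.70 h, the 1-month change 0.35 h instead of 0.75, and the intercept 0.4833 − 0.35 = 0.133 h. z = 0.35/0.146 = 2.40; power 67%.

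*Three-level factor.* Noncentrality = (93.75/4) × (0.75² + 0.70² − 3 × 0.4833²) = 23.44 × 0.352 = 8.24 on 2 df; power 73%.

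**Step 3: the planned analysis set.** The Analytic plan keeps everyone with any data. The same generalised least squares calculation was repeated with all available data from 250, four correlation matrices (equal 0.50; equal 0.45; 0.50 and 0.45 from baseline with 0.50 or 0.45 between follow-ups), nested or independent dropout, and design effects from 1.0 to 1.14.

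| Test | Power | Fitted 12-month change difference (assumed 0.70) | Spurious baseline gap |
|---|---|---|---|
| Slope, months | 26-38% | 0.38-0.42 h (up to 0.44 with independent dropout) | about 0.30 h |
| Slope, wave | 65-77% | 0.73-0.76 h (up to 0.77 with independent dropout) | about 0.10 h |
| Three-level factor, 2 df | 70-81% | not constrained | none |

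A 300-run random-intercept simulation with N = 250 and dropout gave 33% for the slope in months and 75% by wave. For 80% power the slope in months would need about 680 to 870 completers.

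**The case against.** The strongest defence is that the Longitudinal analyses text presents itself as the more specific statement, names the primary-hypothesis test and describes the expected pattern, so it could be read as governing, with the Analytic plan as a loose summary. That is a reasonable guess at intent. It does not resolve the conflict, because a three-level factor is not a refinement of a linear trend.

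The second objection stands in full. A reader might infer that the slope test has only 23-29% power. That requires time in months, completers only, and a design effect of about 1.11. The coding is not stated, the Analytic plan rules out a completers-only primary analysis, and a random intercept for day largely cancels in within-person change. A reader might also infer that the plan as written largely misses the benefit and gives badly biased estimates. That too depends on coding in months: by wave, the fitted 12-month change is close to 0.70 h, the false baseline gap falls to about 0.10 h, and the power loss against the factor test is only a few percentage points. What remains even then is a 1-month change fitted at roughly half its assumed size.

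Third, exact contrasts may be left to an analysis plan that is not shown. That is fair for a missing contrast; it does not cover two conflicting models that the article itself states.

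**Conclusion.** Wrong as written. Two sections specify different tests of the same primary hypothesis, and one imposes a straight line on an effect the trial assumes to be a step. The cost of the linear version depends on a coding the document does not give: about 26-38% power in months, about 65-77% by wave, against about 70-81% for the factor interaction. Under either coding the slope test has less power than the factor test and falls short of the stated 80%. The ranges reflect the unstated correlation between follow-ups, the design effect and the dropout pattern, and they assume two-sided testing and equal arms.

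The documents do not support a single low power figure as a property of the plan, nor any suggestion that the model would be chosen on the results; they only leave that choice open. The factor test is not comfortably powered either: its range mostly lies below 80%.

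**What to change.** Delete the linear time effect from the Analytic plan section and use time as a three-level factor (baseline, 1 month, 12 months) in the primary and secondary longitudinal models. State which group-by-time test governs the primary conclusion, consistent with the Longitudinal analyses section and with the three-time-point scenario C of Table 1, and give its power at N = 250. That statement should be explicit, because the scenario C figure reproduces as a baseline-adjusted mean of the two follow-ups, which is not the 2-df interaction.

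If a 12-month contrast alone were made primary instead, the plan would have to say that N = 250 is below the 314 that Table 1 gives for scenario B.

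Cost: one or two sentences; no change to visits, questionnaires or data collection.

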#### Sunless Tanning Behavior

Participants will be asked to read the following definition of sunless tanning: *Sunless tanning, also known as self-tanning or fake tanning, involves the application of creams, foams, sprays that dye skin a tanned color, or spray tans that you can get at a tanning business. These do NOT include bronzing powders and creams which can be washed off with soap and water*. They will then be asked the open-ended question, "how many times have you used sunless tanning products or spray-on tans in the last month?"

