#### Longitudinal analyses

Consistent with Consolidated Standards of Reporting Trials (CONSORT) guidelines, data on recruitment, participation rates, and drop-out will be collected and reported [40]. Should the frequency of missing data be less than 5%, baseline value carried forward will be conducted with proposed analyses. If the missingness becomes prevalent, the differences in demographic characteristics will be assessed between the completers and the noncompleters to identify possible non-differential missing patterns between intervention groups or demographic subgroups. If missing data appears to be not completely at random, a post-stratification method will be employed to address the issue. Otherwise, missingness will be assumed to be completely at random in the subsequent analyses. Since the data generated in this trial is longitudinal in nature, linear mixed models (LMM) or generalized linear mixed models (GLMM) will be applied to assess intervention effects on continuous and discrete outcomes, respectively [41]. A three-level LMM or GLMM (repeated observations, within subjects, within clusters) will be conducted with individual as the unit of analysis and cluster (day) entered as a random intercepts. Intervention indicators, as well as other key demographic confounders, will be included in the models as fixed effects. Subjects within each cluster will be considered independent from each other. For repeated observations within subjects, an unstructured correlation structure will be used. Finally, a separate set of analyses will be performed on participants who provided complete data. Should completer and ITT analyses yield similar results, the most conservative analysis will be reported. Should analyses yield different results, multiple analyses will be reported.

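### Use of sunless tanning products has two unranked analyses, one of them a completers-only chi-square test that has no cluster term and stops at 1 month

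*Protocol article*

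**What the plan says.** The Abstract, Research goals and Longitudinal analyses all list use of sunless tanning products among the secondary outcomes, without ranking them. It is measured by an open-ended count: "how many times have you used sunless tanning products or spray-on tans in the last month".

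The Analytic plan says: "Chi-square analyses will be used to examine the differences between two conditions for the use of indoor tanning and sunless tanning at baseline". The full timing is "at baseline and then at 1-month follow-up". The analysis set is restricted: "Only participants with complete data at both time points will be included in the chi-square analyses". No adjustment for clustering is mentioned.

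The Longitudinal analyses section sets a general rule: "linear mixed models (LMM) or generalized linear mixed models (GLMM) will be applied to assess intervention effects on continuous and discrete outcomes, respectively". The model is three-level, "with individual as the unit of analysis and cluster (day) entered as a random intercepts". The primary model has "time (baseline, 1 month, and 1 year follow-up) as a within subjects factor", and the text continues: "Secondary outcome variables including sun protection behavior, sunburns, and use of sunless tanning products will be examined in the same way".

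The Randomization section assigns each beach to a condition afresh on each data-collection day. Indoor tanning is measured, but no list of secondary outcomes names it.

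**The concern.** One outcome has two inferential analyses that differ in test, analysis set, time points and handling of clustering, and the protocol does not rank them. If they disagree, either could be presented as the result for sunless tanning, the behavior that the intervention promotes as a substitute for sunbathing.

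An ordinary chi-square also treats the women as independently randomised. Condition is assigned to a beach on a day, and the sample-size section itself allows for correlation among women recruited on the same day. If that correlation acts within a beach-day, the chi-square p-value is too small. In addition, the test does not cover 12 months, and comparing categories of use would mean collapsing an open-ended count for which no cut-off is given.

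**Working it through.** **1. The two plans side by side**

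| Feature | Analytic plan: chi-square | Longitudinal analyses: mixed model |
|---|---|---|
| Times | Baseline, 1 month | Baseline, 1 month, 1 year |
| Women included | Data at both times only | Anyone with at least one time point (Analytic plan, on the mixed model) |
| Cluster term | None stated | Random intercept for day |
| Scale | Use; categories not defined | GLMM if the outcome is discrete |
| Inference | Arms compared separately at each time | Group-by-time interaction |

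No sentence ranks one column above the other.

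**2. The plan's own allowance for clustering**

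The protocol gives no figure for the chi-square tests. The nearest is Table 1, scenario A: difference 0.75, SD 2.0, within-subject correlation 0.50, 16 clusters, 12 women per cluster, ICC 0.01, dropout 0.15, 5% significance (two-sided assumed) and 80% power.

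- Baseline-adjusted formula: n = 2 × SD² × (1 − r²) × (1.960 + 0.842)² / difference² = 2 × 4 × 0.75 × 7.85 / 0.5625 = 83.7 per group.
- Design effect: 1 + (12 − 1) × 0.01 = 1.11, so 83.7 × 1.11 = 92.9, or 93 against the stated 94.
- Total: 2 × 94 / 0.85 = 221.2, against the stated 222.

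The row reproduces closely, so the plan accepts a design effect of about 1.1 for its primary outcome. The chi-square makes no such allowance.

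**3. Type I error of the unadjusted chi-square**

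Inputs: N = 250 (Abstract), 15% loss at 1 month and ICC 0.01 (Sample size), 16 clusters (Table 1). Expected women at 1 month: 250 × 0.85 = 212.5.

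Table 1 labels the cluster as a day. Two readings are possible: 16 clusters in total, or 16 dates with two beaches each, which makes 32 beach-days.

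Formulas: DE = 1 + (m − 1) × ICC; true alpha ≈ 2 × [1 − Φ(1.96/√DE)]. They assume equal cluster sizes, large-sample normality and correlation specific to the beach-day.

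- 16 clusters: m = 212.5/16 = 13.3; DE = 1.123; effective N = 212.5/1.123 = 189; alpha ≈ 0.064.
- 32 clusters: m = 212.5/32 = 6.6; DE = 1.056; effective N = 201; alpha ≈ 0.057.

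**4. Sensitivity to the ICC**

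No ICC is given for sunless tanning; 0.01 was set in planning for sunbathing time. The last two rows are assumptions.

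| ICC | Alpha, 16 clusters | Alpha, 32 clusters |
|---|---|---|
| 0.01 (protocol) | 0.064 | 0.057 |
| 0.02 (assumed) | 0.079 | 0.063 |
| 0.05 (assumed) | 0.123 | 0.084 |

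**5. Direction of the error**

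Both beaches run at the same time, and the Randomization section describes day and weather as held constant across the arms. An effect of the date that is common to both beaches then cancels from the difference between arms, and ignoring it tends to make the test conservative. Only correlation peculiar to one beach on one day inflates the error.

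**The case against.** The strongest defence is that the article already contains a sound analysis. Sunless tanning is to be examined like the primary outcome, in a model with a cluster random intercept and a 1-year assessment; the chi-square is a short-term supplement in a condensed text. Much of this stands, and it removes several stronger readings:

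- A reader might infer that the 12-month effect goes untested. It does not: the mixed model covers it, and only the chi-square stops at 1 month.
- A reader might count three conflicting analyses: chi-square, GLMM and linear mixed model. The linear-model paragraph continues the LMM/GLMM rule and can be read as sharing its group-by-time structure, which leaves two.
- A reader might see a breach of intention to treat. The Analytic plan states that principle for the primary outcome, and completer analyses are expressly planned beside ITT. A woman without a 1-month answer has no 1-month outcome under any method. What remains is that completers are the only set given for the chi-square.
- A reader might extend the contradiction to indoor tanning. That outcome is not a named secondary outcome, and its chi-square conflicts only with the general LMM/GLMM rule.
- A reader might quote an error rate above 10%. That needs an ICC of about 0.05, which the protocol nowhere gives.

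The defence does not supply a ranking. Nothing labels the chi-square as supportive or descriptive. The rule for reconciling completer and ITT results does not clearly cover a different test on a different scale. This is not detail left to a fuller document, because the article itself fixes both methods.

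**Conclusion.** The point holds for sunless tanning: two stated analyses, no order between them, and one that is unsuited to daily assignment of beaches. The absence of a cluster term is inferred from the ordinary form of the test and the lack of any stated adjustment.

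The type I error figures (about 6.4% or 5.7%, depending on the cluster reading) rest on the protocol's ICC of 0.01 carrying over to this outcome, on the planned 15% loss, and on correlation specific to the beach-day. The contradiction depends on none of these. It affects a secondary outcome and leaves the primary analysis untouched, but it should be corrected because it leaves the choice of result open.

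**What to change.** In the Analytic plan, replace the chi-square as an inferential test with one pre-specified main analysis of sunless tanning:

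- the GLMM that the Longitudinal analyses section already prescribes for discrete outcomes;
- one stated form of the outcome, either any use or number of uses, chosen in advance;
- a random effect for beach-day, so that the cluster term matches the unit assigned;
- all available data, with between-arm contrasts at 1 month and at 12 months.

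State in the Longitudinal analyses section that this is the model meant for sunless tanning. Use the same approach for indoor tanning. Any chi-square or baseline comparison may stay if it is labelled descriptive.

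The cost is plan wording and analysis code; no data collection changes. One small downside is that, if use is sparse, only the any-use model may be feasible, which is a reason to settle the form of the outcome beforehand.
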